## D.6. Tasks and approaches

The tasks to accomplish this project are presented below. We further outline our procedures for acquisition and analysis of the study data in section D.9.

### D.6. a. Enrolment of trial villages and study subjects from the rural area covered by the PCI program

Communities in the area earmarked to participate in the SODIS component of the PCI program on "*salud integral*" will be contacted by PCI and the Fundación SODIS. Twenty-two communities will be randomly selected from a list of approximately 50 villages designated to be eligible for SODIS implementation by PCI. For participation in this study, community leaders of the randomly selected communities will be contacted by the study team. This team will approach individual village governments in their communities, describe the study and solicit their participation. If the village leadership indicates interest in participating the team will provide the same information about the trial and associated procedures as is given in the individual consent forms: eligibility criteria for households and study children, design of the study, activities involved when participating, potential risks and benefits.

A list of households with children below the age of five years will be available from information on the village profiles collected for each village covered by the PCI program and from the planned initial screening survey. Children <5 will be randomly selected from this list and subsequently visited by project staff. If the mother/caretaker of the child indicates an interest in participating the project staff will go through the eligibility criteria with the participant using a prepared form (Appendix J). If the mother/caretaker of the child is willing and eligible the project staff will go through the consent form with the mother. The consent form will contain all information about the design of the study, activities involved when participating and potential risks and benefits. Signatures of both parents and all household members living permanently there will be required. If the parents agree to participate and have signed the informed consent form the enrollment questionnaire will be filled out at the participant's home (Appendix J). For illiterate participants, the consent will be read to them and they will be asked to provide permission verbally in front of two witnesses (see also instructions for the consent form in Appendix M). If consent forms cannot be completed during the first visit, field staff will arrange for a follow-up meeting. All information collected from households which are not eligible or decline to participate in the study will be destroyed except for information about exclusion. This information will be used to assess potential biases that might occur from the selection procedure of study subjects. These data will be coded and recorded with no identifying information on the household.

#### **D.6.b. Baseline morbidity surveys in the trial villages to estimate the period prevalence of diarrheal episodes in children <5 years and to facilitate randomization of communities**

At the beginning of the study, a prospective eight week survey among households with children <5 years will be conducted in the 22 villages to estimate the proportion (period prevalence) of child diarrheal illness. The usually short duration of a diarrheal episode and the short incubation period for a new episode will allow us to estimate the incidence density of child diarrhea in each cluster (i.e. village-cluster incidence rate) at baseline. The main purpose of obtaining a prevalence estimate is to facilitate matching of study sites according to the occurrence of reported diarrhea in children. This change (previously a 7 day cross-sectional survey but now an eight week longitudinal measurement) was done in order to address a comment in the prior review about improving our strategy to minimize possible differences in confounding factors between villages at baseline. Sites ranked by eight week baseline diarrhea rates are then grouped in pairs and the introduction of the SODIS intervention is randomly allocated to one of them. Thus, 11 sites receive the intervention, 11 other sites serve as controls. This high level randomization of the village-clusters to the SODIS intervention is the single most effective strategy to limit bias in the estimation of the intervention effect (Murray 1998) (cf. also Section D.7.). PCI will adapt to the random allocation of the SODIS intervention and will start activities in the villages of the intervention arm after our baseline survey has been completed.

Additionally, stool specimens will be collected from a random sample of 220 children during the baseline morbidity surveys. In each community specimens from two children for every one-year age group will be collected (ten total per village). We will obtain one stool specimen at baseline and after 6 months, and also one specimen at the onset of their first diarrheal episode and submit it for microbiologic analysis. Stool analysis at baseline and mid-term will allow us to estimate the pathogen-specific infection rates in asymptomatic cases in both intervention arms. Microbiologic testing of stools of the same cohort will be repeated at mid-point of the project to obtain a repeated measure of infection status (regardless of disease status) at another season. By conducting microbiologic testing of the subsequent 220 symptomatic diarrhea cases we will be able to obtain rates of pathogen-specific diarrheal illnesses and pathogens responsible for the differences in diarrheal illness between intervention and control group (see section D.6g. Specimen collection and testing).

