- *Health outcome and stool laboratory* : In total, 35 (24.6%) of the children were reported experiencing an episode of diarrhea at the time of the interview. The frequency of reported diarrhea steadily decreased from 35.1% in infants (defined as <12 months for this analysis) to 0% in children below 5. ( $p=0.016$ ) (Appendix F, Table below). We successfully obtained stool samples of 80 children and completed microbiological testing in 74 (92.5%) of them (see also Appendix F, Table 2/3.). Bacterial infections were found in 5 children (Salmonella sp 2x, Shigella 1x, E.coli 2x). Protozoal and helminthic infections were recorded in 48.6% (36/74) and less often in symptomatic cases than in asymptomatic cases (OR=0.3, CI=0.08 – 1.11). Diagnostic procedures may explain this finding: 94% of the stool samples of symptomatic children were recorded as liquid in the laboratory. However, same aliquots of liquid and solid fecal matter were used for stool microscopy rendering liquid and thus, diluted stool samples less likely for parasite detection.

Reported child diarrhoea and parasitic infection status of 140 children <5 years from Mizque, Bolivia; 2001

|                                  | Total      | Children's age (months) |           |           |          |         |
|----------------------------------|------------|-------------------------|-----------|-----------|----------|---------|
|                                  |            | 0-11                    | 12-23     | 24-35     | 36-47    | 48-60   |
| Reported diarrhoea status |            |                         |           |           |          |         |
| - Diarrhea                       | 35 (25%)   | 20 (35.1)               | 12 (30)   | 3 (13.6)  | (0)      | (0)     |
| - No Diarrhea                    | 105 (75%)  | 37 (64.9)               | 28 (70)   | 19 (86.4) | 13 (100) | 8 (100) |
| Total                     | 140 | 57                      | 40        | 22        | 13       | 8       |
| Stool diagnostics         |            |                         |           |           |          |         |
| - Entamoeba hist./dispar  | 17 (23.0%) | 2 (7.4)                 | 6 (27.3)  | 4 (26.6)  | 2 (33.3) | 3 (60)  |
| - Giardia lamblia         | 23 (31.1%) | 1 (3.7)                 | 6 (27.3)  | 9 (60)    | 3 (50)   | 4 (80)  |
| - Protozoa                       | 34 (45.9%) | 3 (11.1)                | 10 (45.5) | 12 (80)   | 5 (83.3) | 4 (80)  |

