## D.5. Evaluation of the outcome measures

Evaluation of differences in the primary outcome measure between the active and control arms will be through relative incidence rates of gastrointestinal illness (total episodes of child diarrhea / total person-time of observation in the control group divided by the same measure in the active group) adjusted for the nature of the cluster sampling. Secondary outcomes include child-level outcome measures such as the total number of days with diarrhea, the mean duration of diarrhea, and the number of visits to health care providers caused by the diarrhea. We also will obtain information to allow an analysis using a combination of symptoms that describe 'highly credible gastrointestinal illness' (HCGI) (Payment et al. 1991) from our weekly diarrhea monitoring household interviews (Appendix J).

Outcome data will be collected through a surveillance system established to measure diarrheal morbidity through daily illness diaries kept by the mother/caretakers of the children, and through weekly home-visits by project staff. A standardized questionnaire will be administered covering the clinical signs and gastrointestinal symptoms of current illness. Environmental (household and village-specific characteristics) as well as behavioral traits (water and food handling practices in the home, presence of pets, latrine arrangements) will also be recorded. Weekly home visits result in a total of 52 environmental and morbidity recording sheets for each child in the study.

Stool specimens will be collected and submitted for microbiologic analysis from a sub-sample of 220 (33%) of the children in the study during baseline, at their first diarrheal episode. In addition, as suggested by the reviewer, the entire sub sample will also be re-examined at a fixed time (at 6 months of follow up). This will allow us to measure three additional pathogen-specific outcomes: the prevalence of asymptomatic infections; the proportion of diarrhea attributable to infection for each organism detected in the study; and differential (pathogen-specific) infection rates in intervention and control group.

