#### **D.6.g. Specimen collection and testing (stool and water specimens)**

An important component of our proposal is the collection and microbiological testing of stool specimen from study children. Data collection on pathogen-specific infections will be generated to elucidate three issues of particular interest in the current setting : i) the prevalence of asymptomatic bacterial, viral and parasitic infections in rural Bolivian children, ii) the proportion of diarrhea attributable to infection in the different treatment arms, and iii) the pathogen-specific attributable risk for diarrhea.

Prevalence of asymptomatic infection is obtained through the microbiologic testing of the random sample of 220 children at baseline. We will calculate the proportion of pathogen-positive stool samples among those children that were not classified as diarrhea. To obtain the proportion of diarrhea attributable to infection test results will be pooled from all symptomatic cases identified at baseline and at the time of their first episode. Since this will partly involve repeated measurements of the same individual we will account for the possible intra-person correlation by applying General Estimation Equation (GEE) approaches in the analysis (Zeger et al. 1988) (see also section D.9.). We will also explore how individual pathogen might be related to the probability of diarrhea.

These specimens will be tested for common causes of gastrointestinal illness due to viruses, bacteria and parasites. Stool specimens will be collected at baseline from a random sample of the children under five (N=220) and again at their first symptomatic episode later in the study. At the reviewers suggestion we will repeat testing the same cohort (regardless of disease status) at mid-point of the project. Field staff will distribute stool collection kits in the morning and collect them in the evening from the households if the child cannot produce a sample at the time of the visit. They will store the specimen in cooler boxes at 4 degrees C. and transport them to the local research office where refrigeration is possible. From there they are transferred to the central laboratory in Cochabamba within 48 hours. Participants will be notified by the study team about the test results and treatment initiated upon consultation with the medical center. A comprehensive array of tests will be performed at the Medical Faculty of the University of San Simon in Cochabamba.

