Multivariate statistics: Simple comparisons of rates will be done using software that is designed to accommodate the complexity of a cluster randomization design (SUDAAN). Simple Poisson regression cannot be used to make inferences about the effect of treatment in cluster randomization trials since it is constructed on the assumption that the conditional responses of individuals are statistically independent. An extension of the Poisson regression, generalized estimation equation approach (GEE) will be employed (Liang and Zeger 1986). For these regressions, the number of episodes of diarrhea for each child will be the outcome and, although we will report the inference based on robust estimates of the variance, we will assume the correlation within a cluster to be compound symmetry in the estimation procedure. We can possibly reduce the variance of the estimate of the treatment effect by adjusting for both baseline risk factors measured at either cluster level (cluster size, SES) or individual level (e.g. age, sex) (Klar et al. 1995). This becomes particularly important if the distribution of these covariates, by bad luck, are not similarly distributed in the treatment and the control arms of the study. We will also explore the strength of possible effect modification by looking at the inference of multiplicative interaction terms discussed above. We will account for the fact that some children will have different total time at risk due to our definition of an episode discussed in Section D.3 by including an offset term in the regression models that is the natural log of the total time (in days) that a child was at risk of diarrhea. Finally, the regression model will return parameters that can be interpreted as the marginal ratio of diarrhea rates relative to the variable of interest. Specifically, the models will return an estimate of the ratio of diarrhea rates in populations that have the treatment versus those with the controls, all other factors (covariates) being equal in the two populations. If we find significant effect modification with treatment, then the model will return rate ratios specific to levels of the interacting variable(s), e.g., the ratio of rates in treatment versus control among populations with unsanitary facilities.

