A secondary analysis will consider estimation of the attributable fraction of diarrhea due to specific pathogens. In this case, the outcome data is the presence or absence of diarrhea among the stool samples and the explanatory variables of interest are the presence/absence of particular pathogens. In this case, we have two levels of replication: 1) the possibility of more than one stool sample (diarrhea) per child and 2) 10 children (with specimen tested) within the

cluster (village). Given the very real possibility residual correlation among the replicates, we again will use a GEE regression approach. In this case, our outcome is binary (presence/absence of diarrheal stool sample) so we will use the GEE generalization of logistic regression. We will choose the variables to adjust for (and those to consider as effect modifiers) similar to that described above (note, that treatment now plays the roll of a potential effect modifier).

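### The pathogen–diarrhea model borrows a covariate rule under which age is optional, and the age-stratified stool subsample is summarised by a crude proportion, although pilot parasite data show strong, opposite age gradients

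*Protocol*

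**What the plan says.** Section D.6.b introduces the subsample as random: "stool specimens will be collected from a random sample of 220 children during the baseline morbidity surveys". It then sets the allocation: "In each community specimens from two children for every one-year age group will be collected (ten total per village"). Sections D.1 and D.6.g also call the 220 children a random sample, and Section D.5 gives its share of the cohort: "sub-sample of 220 (33%) of the children in the study during baseline".

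Section D.6.g fixes the estimator for asymptomatic infection: "We will calculate the proportion of pathogen-positive stool samples among those children that were not classified as diarrhea". To find how much diarrhea is due to infection, the same section says that "test results will be pooled from all symptomatic cases identified at baseline and at the time of their first episode". GEE handles repeated samples from one child. Neither age nor sampling weights are mentioned.

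For the logistic GEE of diarrhea on pathogens, Section D.9 says: "We will choose the variables to adjust for (and those to consider as effect modifiers) similar to that described above". The rule it points back to belongs to the treatment comparison: "We can possibly reduce the variance of the estimate of the treatment effect by adjusting for both baseline risk factors". Age appears there only as an example, and adjustment is said to matter particularly when covariates differ between arms.

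In the pilot (Section C.1, iv), infection was less frequent in symptomatic children, with an odds ratio of 0.3. The text offers one explanation: "Diagnostic procedures may explain this finding: 94% of the stool samples of symptomatic children were recorded as liquid in the laboratory". Age is not considered, although the table beside it breaks both infection and diarrhea down by age.

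**The concern.** The rule in Section D.9 suits a randomised treatment: covariates are balanced in expectation, so adjustment mainly buys precision or repairs chance imbalance. In the pathogen model the exposure is infection, which nobody randomised, and treatment is only a possible effect modifier. Balance between arms says nothing about whether age confounds infection and diarrhea. Under the borrowed rule, well-balanced arms would weaken the case for adjusting, even where confounding by age is strong.

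The equal age quota has a separate consequence. A crude proportion from it estimates prevalence in a population with equal numbers at each year of age. Whether that is the population of interest is not stated.

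At stake are the pathogen-specific results of the second specific aim (Section A). An odds ratio confounded by age could lead a parasite with no effect, or a moderately harmful one, to be reported as protective, and its attributable risk to be understated.

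**Working it through.** **The plan's own figure.** 2 children × 5 age groups × 22 villages = 220, and 220/660 = 33%. Both agree with the protocol.

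**Inputs** (pilot table, Section C.1, iv):

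| Age (months) | Children | Diarrhea, d | Any parasite, p |
|---|---|---|---|
| 0–11 | 57 | 20/57 = 0.351 | 3/27 = 0.111 |
| 12–23 | 40 | 12/40 = 0.300 | 11/22 = 0.500 |
| 24–35 | 22 | 3/22 = 0.136 | 13/15 = 0.867 |
| 36–47 | 13 | 0 | 5/6 = 0.833 |
| 48–60 | 8 | 0 | 4/5 = 0.800 |

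The 12–23 month stool column shows 22, but its parts sum to 21 (11 + 10). Results with 21 are given in brackets.

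**Odds ratio from age alone.** Assume no association within any age group, so the probability of both is p × d. With age weights w, OR = [Σw·p·d × Σw(1−p)(1−d)] / [Σw·p(1−d) × Σw(1−p)d].

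- Equal quota (w = 1 in each group): 0.307 × 1.409 / (2.804 × 0.480) = **0.32** (0.33).
- Pilot ages (w = number of children): 10.82 × 53.19 / (51.81 × 24.18) = **0.46** (0.47).

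**A harmful parasite.** Suppose the true odds ratio is 2 within every age group. For each group the joint probability a solves a(1−p−d+a) = 2(p−a)(d−a), giving 0.055, 0.186, 0.126, 0, 0. Summed over equal quotas, the four cells are 0.367 (both), 2.744 (infection only), 0.420 (diarrhea only) and 1.469 (neither). The crude OR is 0.367 × 1.469 / (2.744 × 0.420) = **0.47**. A doubling of the odds would read as a halving.

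**Asymptomatic prevalence**, Σw·p(1−d) / Σw(1−d):

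- Equal quota: 2.804/4.213 = **67%** (67%).
- Pilot ages: 51.81/105 = **49%** (50%).
- Flat target ages: the quota is proportional to the target, so there is essentially no shift.
- By organism, quota against pilot ages: *Giardia* 48% against 32%; helminths 10% against 9%. For helminths the age-only OR under the quota is 0.95–0.97.

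**Can the quota be filled from 30 children?** P(fewer than two in a group) = (1−q)^30 + 30q(1−q)^29. With q = 8/140 for ages 48–60 months this is 0.48; with flat ages, q = 0.20, it is about 0.01.

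**Cost of standardising to the pilot ages.** Design effect = 5 × Σw² (w as proportions) = 5 × (57² + 40² + 22² + 13² + 8²)/140² = 5 × 5566/19600 = 1.42. The 220 children then carry the information of about 155, and intervals widen by √1.42 = 1.19.

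**Limit of the calculation.** It describes one survey, such as baseline or month 6. The planned model also uses stools from each child's first episode. If most children of all ages have an episode, diarrheal specimens are spread more evenly over age and the distortion is smaller. The documents do not allow that to be computed.

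**The case against.** **Age adjustment is allowed, and the details belong in an SAP.** Section D.9 does name age as a possible covariate, and an SAP not shown here may fix it. What stands against the protocol is the criterion it states for choosing: one built for a randomised exposure and applied to one that is not.

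**Random sample and age quota do not conflict.** Read together, the two sentences in Section D.6.b describe an age-stratified random sample, openly disclosed. This is fair; the label is imprecise, and the design itself is sound.

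**The prevalence benchmark is uncertain.** This also stands. The pilot table has 140 children from 142 families, although 54.3% of families had more than one child under five, so its 41% share of infants need not represent all under-fives. The trial's own age mix is unsettled: Section D.1 enrols the youngest child of a family, while Sections D.2 and E.4 enrol all children under five. The objection does not rescue the odds ratio: flat ages remove the prevalence shift but leave the age-only odds ratio at about 0.32.

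**Stronger readings.** A reader might infer that the pathogen outcomes mainly reflect age. The documents do not support this: age-specific data exist only for parasites, helminths barely move, no gradient is given for bacteria or viruses, and the infection comparison between arms (Section D.5) uses the same quota in both arms. A reader might also infer that age explains most of the pilot's odds ratio. Its interval, 0.08 to 1.1, is too wide to apportion, and diarrhea by age among the 74 tested children is not reported. Nor can one say that half the villages will miss the quota; the figure ranges from about 1% to 48% with the age mix.

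**Conclusion.** The point holds for protozoa and for any parasite. Leaving age optional in the pathogen–diarrhea model is a mistake in the stated rule. On the pilot rates, age alone gives a crude odds ratio of about 0.32 under equal quotas and 0.46 under the pilot ages. The need to adjust does not depend on the cohort's age mix.

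The prevalence point is conditional: a shift of about 17 percentage points (67% against 49–50%) if the target ages resemble the pilot's, and essentially none if they are flat.

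These sizes assume that the pilot rates carry over, that diarrhea by age in 140 children applies to those giving stools, and a single-survey specimen set. The oldest cells hold five or six stools, so the figures are indicative. The issue affects a secondary aim; the primary comparison of diarrhea incidence is untouched.

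**What to change.** 1. In Sections D.1, D.6.b and D.6.g, describe the subsample as age-stratified with equal allocation, and state what happens when a village lacks two children in an age group.
2. In Section D.9, make one-year age group a required covariate in the pathogen–diarrhea GEE models, whatever the balance between arms.
3. In Section D.6.g, report asymptomatic prevalence by age group and standardised to a named target age distribution. First reconcile Section D.1 with Sections D.2 and E.4 on which children are enrolled.

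No new data are needed, since the sampling already requires each child's age. Standardised prevalence will have wider intervals: a design effect of up to about 1.4 (intervals about 19% wider) if the target is the pilot age mix, and close to none if the target is flat.

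### The pathogen analyses stated for the stool subsample give shares and associations, not the pathogen-specific diarrhea rates by arm that D.6.b promises

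*Protocol*

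**What the plan says.** **Sampling.** D.6.b states that "stool specimens will be collected from a random sample of 220 children during the baseline morbidity surveys", ten in each village. It allocates villages equally: "Thus, 11 sites receive the intervention, 11 other sites serve as controls". The same children give stool again at six months and "also one specimen at the onset of their first diarrheal episode and submit it for microbiologic analysis". D.1, D.5 and D.6.g describe the same scheme. No section provides for testing second or later episodes.

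**Promise.** Section A makes it a specific aim to identify which pathogens account for the difference in diarrhea between the arms. D.6.b says how. It counts on 220 later symptomatic cases being tested and expects from them that "we will be able to obtain rates of pathogen-specific diarrheal illnesses and pathogens responsible for the differences in diarrheal illness between intervention and control" groups. D.5 lists a related outcome, "differential (pathogen-specific) infection rates in intervention and control group".

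**Stated pathogen analyses.**
- D.6.g plans the pathogen-positive proportion among non-diarrheal stools. It also plans the share of diarrhea that infection explains, by arm, pooling symptomatic children found at baseline with first episodes.
- D.9 plans a GEE logistic regression of diarrheal versus non-diarrheal stool on pathogen presence, with the remark "note, that treatment now plays the roll of a potential effect modifier".

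The log time-at-risk offset in D.9 belongs to the all-cause Poisson model. Neither pathogen analysis uses child-time or diary incidence.

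**The concern.** A rate needs a numerator that responds to incidence and a denominator of time. Taking one specimen at the first episode nearly fixes the numerator: when almost every child has at least one episode in 12 months, almost every child supplies exactly one case specimen, in either arm. A threefold or fivefold yearly burden gives much the same count.

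What remains in the specimens is the pathogen mix, and a mix can mislead. If SODIS removes some causes, the causes it does not touch make up a larger share of what is left. Read by arm, those pathogens would appear to increase under SODIS. A pathogen reduced in line with all the others would show no change. The point is practical, because C.1 itself reports that SODIS may not inactivate *C. parvum* well. A named specific aim is at stake; the primary outcome is not.

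**Working it through.** **Inputs.** 22 villages, ten sampled children each, 11 villages per arm (D.6.b); 12 months of follow-up (D.1); 5 versus 3.33 episodes per child-year (D.8). The pathogen splits and gamma shapes below are assumptions.

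1. **The plan's figure.** 22 × 10 = 220 children, 220/660 = 33%, and 110 per arm. Under a constant Poisson rate R, expected first-episode specimens per arm = 110 × (1 − exp(−R)).
   - Control: 110 × (1 − exp(−5)) = 109.3.
   - SODIS: 110 × (1 − exp(−3.33)) = 106.1.
   - Total 215.3, within 3% of the 220 in D.6.b.

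2. **Information on incidence.** The count ratio is 106.1/109.3 = 0.97; the true rate ratio is 3.33/5 = 0.67. Testing every episode would give 110 × 5 = 550 and 110 × 3.33 = 367 specimens, so about 20% and 29% of episodes are tested.

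3. **Sensitivity of the count ratio over 12 months.** With gamma variation between children, P(at least one episode) = 1 − (1 + R/shape)^(−shape).

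| Assumption | Control | SODIS | Ratio |
|---|---|---|---|
| 5 vs 3.33, no variation | 109.3 | 106.1 | 0.97 |
| 5 vs 3.33, shape 2 | 101.0 | 94.5 | 0.94 |
| 5 vs 3.33, shape 1 | 91.7 | 84.6 | 0.92 |
| 5 vs 3.33, shape 0.5 | 76.8 | 70.3 | 0.92 |
| Control rate 4, no variation | 108.0 | 102.4 | 0.95 |
| Control rate 4, shape 0.5 | 73.3 | 66.3 | 0.90 |
| Rates by age scaled to the pilot table in C.1 | 65.7 | 64.7 | 0.98 |

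4. **What shares show.** Suppose control has 2 bacterial and 3 other episodes per child-year, and SODIS has 0.33 and 3.
   - Share of other: 3/5 = 0.60 versus 3/3.33 = 0.90, a ratio of 1.5.
   - Specimens: 0.60 × 109.3 = 65.6 versus 0.90 × 106.1 = 95.5, 46% more under SODIS. With gamma shapes 2 to 0.5 the excess is 37% to 40%.
   - True rate ratio for other: 3/3 = 1.00.
   - Conversely, if SODIS cuts every pathogen by a third, one causing 20% of control episodes also causes 20% under SODIS. The share ratio is 1.00; the true rate ratio is 0.67.

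5. **Share × all-cause diary incidence.** 0.60 × 5 = 3.0 and 0.90 × 3.33 = 3.0, which is correct. This also holds with variation between children, provided the pathogen mix does not depend on a child's own rate.

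6. **First episodes ÷ child-time to first episode.**
   - With constant rates, child-time is 109.3/5 = 21.9 and 106.1/3.33 = 31.8 years. Other: 65.6/21.9 = 3.0 and 95.5/31.8 = 3.0.
   - With gamma shape 1, child-time is 110 × ln(1 + R)/R = 39.4 and 48.4 years. All-cause rates are 2.325 and 1.749, ratio 0.75 (true 0.67). Other: 0.60 × 2.325 = 1.395 and 0.90 × 1.749 = 1.574, ratio 1.13 (true 1.00).
   - For shapes 2, 1 and 0.5 the all-cause ratios are 0.71, 0.75 and 0.80, and the ratios for other are 1.07, 1.13 and 1.20.

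**The case against.** The strongest reply is that the protocol collects everything needed and that only a formula is unstated, which an SAP could supply. Several parts of that reply stand.

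- A reader might infer that logistic regression is the only pathogen analysis. It is not: D.6.g also plans proportions by arm, and the D.9 model is presented as estimating attributable fractions.
- A reader might infer that the protocol will compare raw specimen counts. No section says so. The counts above show how little incidence information the specimens hold; the misreading that the plan invites is of shares.
- A reader might infer that the D.5 outcome also fails. It speaks of infection, and the six-month stools, taken from the whole subsample whatever the child's disease status, can serve that comparison.
- A reader might infer that the design makes pathogen-specific rates impossible. It does not, as steps 5 and 6 show. The microbiology paragraph of the introduction to the revised application also says that stool results will be related to the diaries, although it gives no rate.

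The reply fails on one point. D.6.b makes a positive claim, and D.6.g and D.9 name the methods. Followed as written, those methods give shares and associations, and the shares move for pathogens whose rates do not change. That is a mismatch between a specific aim and its stated analysis, not merely an omitted detail.

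**Conclusion.** The point holds for the stated analysis, not for the design, and for the 220 sampled children, not all 660. First-episode testing gives nearly equal case specimens by arm: 0.97 at the planning rates and roughly 0.90 to 0.98 over the 12-month scenarios tried, against a true rate ratio of 0.67. The stated analyses do not restore the missing incidence. In the assumed example, an unaffected group of pathogens goes from 60% to 90% of case specimens at an unchanged rate of 3.0; the size depends on that split, the direction does not. The correction is worth making, although the primary result is unaffected.

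Two qualifications apply. The near-match to 220 relies on constant rates; with variation between children or pilot-like age patterns, about 130 to 196 children would supply a case specimen, but the arms stay close. The specimen text also needs reconciling: D.9 allows more than one diarrheal sample per child (which fits baseline plus first episode), and E.5 gives about 250 symptomatic cases rather than 220. Neither says that later episodes are tested.

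**What to change.** Amend D.9, and align D.6.b and D.6.g with it:

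1. Estimate pathogen-specific diarrhea incidence by arm as the pathogen share among follow-up first-episode specimens multiplied by that arm's all-cause diary incidence. Exclude symptomatic cases found at baseline, which precede the intervention.
2. Compare arms by rate difference and rate ratio, with intervals that respect village clustering and carry the uncertainty of both factors.
3. As a sensitivity analysis, report pathogen-positive first episodes divided by child-time to first episode, noting its bias when rates vary between children.
4. Keep the logistic GEE for the pathogen-diarrhea association only.
5. State the specimen scheme and expected number once, and use it throughout.

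The cost is wording and analysis time. Daily diaries and weekly visits (D.6.c) already supply incidence and episode dates, and no extra specimens are needed.

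The downside must be stated: the main estimate assumes that first episodes represent later ones. At the planning rates the median first episode falls at about 7 weeks (control) and 11 weeks (SODIS), and 81% and 67% of children have had one within four months. D.6.e gives SODIS implementation periods of 4-6 months, so first episodes may reflect early uptake and only some seasons.
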